## **1. Research Title, Main Funding**

Title: Magnetic Seizure Therapy for Bipolar Mania

Funding: Science and Technology Commission of Shanghai Municipality  
(17411969900)

## **3. Study Objectives**

(1) To develop a Magnetic Seizure Therapy (MST) treatment protocol for patients with bipolar mania

(2) To investigate MST induced changes of brain plasticity and cognitive functions in patients with bipolar mania.

(3) To identify biological biomarkers for predicting the MST efficacy and its underlying mechanism

## **4. Background**

### **4.1 Current treatments for bipolar mania**

Bipolar disorder (BD) is characterized by cycling between manic and depressive states. A manic episode, specifically, is a feature of bipolar disorder where an individual experiences heightened mood. The lifetime prevalence of BD is 1% [1], with onset often occurring during adolescence. The resulting years of life lost due to disability rank the eighth among all diseases and the third among mental disorders in low- to middle-income countries [2]. Even during periods of remission, individuals with BD may still experience significant declines in cognitive function and quality of life [3]. Systematic reviews indicate that electroconvulsive therapy (ECT) is a crucial treatment modality for BD, particularly in cases of severe or treatment-resistant conditions [4].

ECT delivers electrical stimulation directly to the brain which induces seizure

activity and achieves therapeutic effects. It is widely used in the treatment of various mental disorders, including mood disorders (major depressive disorder and bipolar disorder) and schizophrenia [5]. However, due to the poor conductivity and significant shunting of the skull, the stimulus intensity applied in ECT is often high and challenging to focus on a specific area. Moreover, it frequently passes through deep brain structures such as the hippocampus and thalamus, leading to noticeable side effects of ECT, particularly cognitive impairments like orientation disorders and memory deficits [6]. In recent years, considering the adverse impact of ECT on patients' neurocognitive function, the U.S. FDA is contemplating categorizing it as a Class 2 (general controls and special controls) or Class 3 (general controls and premarket approval) medical technology [7].

## **4.2 Development of MST**

Since the 1980s, the international community has developed repetitive transcranial magnetic stimulation (rTMS) technology. Leveraging the physics of electromagnetic conversion, this technique initially converts the electrical current into a transient pulsatile magnetic field. This magnetic field can then effortlessly penetrate the skull, reach the cerebral cortex, and generate induced current. TMS is a safe and non-invasive intervention which does not induce seizure. During TMS treatments, patients are awake with no significant discomfort [8]. Later, scientists have developed MST technique that deliberately induce seizures with high-intensity and high-frequency magnetic stimulations around the year 2000 [9].

MST is a novel treatment that induces seizures through the rapid and strong magnetic field. Because the magnetic field easily penetrates the skull, it can selectively stimulate a specific site and only excite the local cortex, inducing seizures by exciting the local cortex. In comparison to ECT, during the process of inducing seizures, MST may not have a direct current passing through deep brain structures (such as the hippocampus and thalamus). Therefore, the side effects of MST may be less than those of ECT [10]. Since 2000, MST has been applied in the clinical treatment of patients with major depressive disorder and bipolar depression. The findings suggest that MST has efficacy comparable to ECT. In addition, the cognitive side effects which are associated with ECT, are less or milder with MST treatment [9]. However, there is currently no research exploring the use of MST as an adjunctive treatment for bipolar manic.

## **4.3 The Mechanism of ECT and MST Treatments**

Although ECT treatment has a history of more than eighty years, the therapeutic

mechanisms for treating manic episodes are far from clear. Initiating this project provides us with an opportunity to investigate the biological mechanisms of ECT and MST interventions. Evidence in this regard will support the future optimization of ECT and MST treatment techniques.

We propose a hypothesis that MST may improve GABA-mediated cortical inhibition (CI) deficits in patient. ECT may significantly increase the seizure threshold in patients by inducing seizures, thereby strengthening cortical inhibitory function [11]. A typical ECT treatment course usually involves 8-10 sessions within approximately a month. As the number of ECT treatments accumulates, the seizure threshold of patients continues to rise. The required stimulus intensity to induce seizures also gradually increases. In comparison to the initial treatment, the intensity required for seizures in the final treatment session often needs to be increased by 50% to 100%.

The CI function can be assessed using TMS, reflecting the inhibitory GABA-mediated cortical response [12]. Research on CI function in patients with schizophrenia has yielded relatively stable results by cortical silent period (CSP), short-interval cortical inhibition (SICI), and intracortical facilitation (ICF). Previous studies have demonstrated reduced CI function in BD patients, reflecting an inhibitory deficit [13].

CI can also be assessed using magnetic resonance spectroscopy (MRS) to identify changes in in-vivo GABA levels in BD individuals [14,15]. However, there is currently a lack of longitudinal reports on changes in GABA levels in BD patients related to ECT or MST interventions. We believe that relying on TMS-derived cortical inhibition indicators and GABA levels detected through MRS technology will provide reliable evidence for mutual validation.

CI function can also be assessed in vivo by magnetic resonance spectroscopy (MRS), reflecting the GABA levels. Previous MRS studies have suggested altered GABA levels in BD individuals [14,15]. However, there is currently a lack of longitudinal studies reporting changes in GABA levels in BD related to ECT or MST. We hypothesize that CI indices measured by TMS and GABA levels measured by MRS will provide more evidence for the underlying mechanism of ECT and MST treatments.

#### **4.3.2 The MST Effect on Resting-state Brain Network**

Functional MRI (fMRI) provides a way to observe the brain fluctuation associated with individual states and information processing. Resting-state fMRI reflects the spontaneous functional activity of the central nervous system in its baseline state, and existing studies support the theory of disrupted cortical-limbic connectivity in patients

with bipolar disorder [17]. Hence, the application of resting-state brain networks is a potential tool to uncover the biological mechanisms of MST treatment in BD, but such study remains rare.

#### **4.4 The Hypothesis of the Present Study**

ECT and MST may have comparable efficacy for treating bipolar mania. There may be common mechanism of the efficacy that results from enhanced CI and the plasticity of functional connectivity. However, MST may have less side effects than ECT due to that magnetic stimulations may not pass the deep subcortical regions.

MST has been a novel treatment for MDD, bipolar depression and schizophrenia. However, there is no clinical trial for MST in bipolar mania. The present study aims to conduct a randomized controlled clinical trial to compare MST and ECT efficacy in bipolar mania. We also will explore the biological mechanism of MST treatments by combining GABA measures and resting-state functional connectivity.

### **5. Experimental Design: Randomized Controlled Study**

Randomization Method: A random number sequence will be generated and recorded by the computer, with each random number corresponding to a specific group (A for ECT group or B for MST group). Patients meeting the inclusion criteria will be assigned to either Group A or Group B based on the random number corresponding to their serial number.

### **6. Participants**

This study plans to recruit 60 patients with bipolar manic for receiving MST and ECT treatments. Additionally, 30 healthy controls will be recruited without any intervention.

#### **6.1 Healthy controls**

Healthy controls will only participate in baseline cognitive function assessment (rBANS), cortical inhibition (including TMS and MRS detection), and resting-state fMRI assessments. They will not receive MST or MST treatments and not participate in follow-up assessments.

The healthy control will give written consent before participating in the assessments. They will be matched with the patient group in terms of sex, age (between

18 and 55 years), years of education, and socio-economic status. In addition, they will be screened to exclude an occurrence of psychiatric disorders by the DSM-5 diagnostic criteria. They have no family history of psychiatric disorders, no history of substance dependence, are not currently taking any medication, and do not have any concurrent major physical illnesses.

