## 8. MST and ECT Procedures

General anesthesia was administered for each participant before each ECT/MST

session by administering propofol (1.82-2.44mg/kg) and etomidate (0.21-0.3mg/kg). The succinylcholine (1mg/kg) was used for muscle relaxation to prevent fractures and other injuries, and the atropine (0.5mg) was used for reducing respiratory secretions. After each ECT/MST session, patients stayed under observation for half an hour and were not allowed to eat until two hours later.

**MST Procedure:** Patients completed 2 or 3-session MST on alternate days every week and achieved 8-10 sessions accumulatively within 4 weeks. MST was administered using the MagPro X100 device with a twin coil (Twin Coil-XS, MagVenture A/S, Denmark) placed and centered on the vertex. The intensity was at 100% device output with 75 Hz frequency. The duration of magnetic stimulations was determined by a titration method until a proper seizure (seizure duration  $\geq 15$  s) was generated. The duration started from 4 s and was increased by 4 s or 8 s up to a maximum of 20 s.

**ECT Procedure:** Patients completed 2- or 3-session MECT on alternate days weekly and accumulated 8-10 sessions within 4 weeks. ECT was performed using the Thymatron System IV device (Somatics, USA) with electrodes placed over the bilateral temporal cortex. The electrical stimulation wave width was at 1.0 ms. The energy of electrical stimulation was determined according to the patient's (age  $\times 0.8 \times 100\%$ ). The energy percent was increased by 5% until a proper seizure (seizure duration  $\geq 25$  s).

**EEG Recording:** During each MST/ECT session, patch electrodes were placed in the bilateral frontal regions to record electroencephalogram (EEG). The epileptiform discharge times induced by MST/ECT were recorded as the effective seizure duration.

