### **9.2.2 Neurocognitive outcomes**

Neurocognitive function were evaluated using the Repeatable Battery for the Assessment of Neuropsychological Status (RBANS) [2]. We used the Chinese version of RBANS, which has good reliability and validity [3], consisting of 12 tasks for five cognitive domains: Immediate Memory (IM), Visuospatial / Constructional (V/C), Language, Attention, and Delayed Memory (DM). A trained staff operated the RBANS assessment. Some participants did not complete the RBANS assessments due to emotional instability and behavioral incooperation in the acute phase. MADRS total scores, RBANS total scores, and scores of each RBANS cognitive domain were secondary outcomes.

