### 360 **14.2 Statistical Analysis Plan**

361 We will use SPSS for statistical analysis, employing statistical methods such as t-  
362 tests, analysis of variance, and correlation analysis based on the data types and  
363 distribution characteristics. For the MRS data, LC-Model will be utilized. After  
364 preprocessing, resting-state fMRI data will be analyzed using software packages such  
365 as REST and GIFT.

366 (1) Baseline comparisons: To compare the differences in neurocognitive function,  
367 CI indicators, and resting-state fMRI measures between the MST group, ECT group  
368 and healthy control group; To explore the correlation between CI indicators and GABA  
369 levels detected within each group.

370 (2) Longitudinal comparisons: Compare the longitudinal changes of clinical,  
371 neurocognitive and CI measures before and after ECT and MST interventions.

372 (3) fMRI: the medial prefrontal cortex within the default mode network (DMN)  
373 will be chosen as a seed to calculate its functional connectivities the posterior cingulate  
374 gyrus, precuneus and the bilateral inferior parietal lobules. We hypothesize that patients  
375 with bipolar mania may show enhanced connectivity within the DMN, and this  
376 connectivity will be improved after MST or ECT intervention.

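### The cognitive objective claims change induced by MST, but the plan names only before/after RBANS comparisons and retests no untreated group, so within-arm change cannot be attributed to MST

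*Protocol*

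**What the plan says.** Protocol section 3, objective 2, reads "To investigate MST induced changes of brain plasticity and cognitive functions in patients with bipolar mania". It names one arm and makes no reference to ECT.

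Section 6.1 limits the untreated group to a single assessment: "Healthy controls will only participate in baseline cognitive function assessment (rBANS), cortical inhibition (including TMS and MRS detection), and resting-state fMRI assessments". It continues: "They will not receive MST or MST treatments and not participate in follow-up assessments". In section 14.2 the healthy controls appear only in the baseline comparisons.

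Section 8 gives both arms the same course. For MST: "Patients completed 2 or 3-session MST on alternate days every week and achieved 8-10 sessions accumulatively within 4 weeks". For ECT: "Patients completed 2- or 3-session MECT on alternate days weekly and accumulated 8-10 sessions within 4 weeks".

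Section 9.2.2 names the instrument ("We used the Chinese version of RBANS, which has good reliability and validity") and its standing: "MADRS total scores, RBANS total scores, and scores of each RBANS cognitive domain were secondary outcomes". It also reports that some participants could not complete the battery in the acute phase. It does not say which test form is used at the second assessment.

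Section 14.2 item "2) Longitudinal comparisons: Compare the longitudinal changes of clinical" goes on to cover the neurocognitive and cortical inhibition measures, before and after ECT and MST. No MST-versus-ECT contrast of RBANS change is named.

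**The concern.** The objective is causal and concerns MST alone, while the analysis named for it is a before/after comparison. Patients enter in an acute manic episode and are retested after a course of at most 4 weeks. Over that interval RBANS can rise for reasons unrelated to MST: familiarity with the tasks, recovery that would have occurred anyway, and other treatment given alongside (sections 4.2 and 7 describe MST as adjunctive). No group in the design isolates these components within the MST arm.

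Two misreadings follow if the plan is carried out as written. A within-arm rise may be reported as a cognitive effect of MST. A flat within-arm result may be reported as absence of harm when a real loss has been offset by the other components. Milder cognitive side effects are the stated rationale for MST (sections 4.1, 4.2 and 4.4), so the second misreading matters more.

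**Working it through.** **No plan figure to reproduce.** The protocol gives no RBANS effect size, retest correlation or power. The one usable figure is 30 patients per arm (section 7), which was not derived from RBANS.

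**Inputs**
- From the protocol: 30 per arm; a course within 4 weeks. The retest interval of about 4 weeks is inferred from the course length, as the text gives no RBANS visit window.
- Assumed: practice gain g of 0.2 to 0.4 baseline SD; test-retest correlation r of 0.6 to 0.8; 20 to 30 completers per arm, because section 9.2.2 reports incomplete RBANS testing.

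**Step 1: within-arm test with no treatment effect.** With equal SD at both tests, set to 1, the SD of change is √(2(1−r)). A paired t-test on n patients has noncentrality g√n / √(2(1−r)). The probability of a significant improvement is the upper tail of the noncentral t beyond the two-sided 5% critical value.

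- Example: n = 30, r = 0.7, g = 0.3. SD of change = √0.6 = 0.775; noncentrality = 0.3 × 5.477 / 0.775 = 2.12; critical value 2.045; probability 0.536.
- Lowest corner: n = 20, r = 0.6, g = 0.2. SD of change = √0.8 = 0.894; noncentrality = 0.2 × 4.472 / 0.894 = 1.00; critical value 2.093; probability 0.156.
- Highest corner: n = 30, r = 0.8, g = 0.4. SD of change = √0.4 = 0.632; noncentrality = 0.4 × 5.477 / 0.632 = 3.46; probability 0.917.

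| Completers | r | g = 0.2 | g = 0.3 | g = 0.4 |
|---|---|---|---|---|
| 30 | 0.8 | 0.388 | 0.709 | 0.917 |
| 30 | 0.7 | 0.277 | 0.536 | 0.780 |
| 30 | 0.6 | 0.219 | 0.427 | 0.658 |
| 20 | 0.8 | 0.269 | 0.521 | 0.765 |
| 20 | 0.7 | 0.194 | 0.376 | 0.592 |
| 20 | 0.6 | 0.156 | 0.296 | 0.476 |

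The nominal value in this direction is 0.025. A gain of only 0.1 SD with n = 30 and r = 0.6 still gives 0.09. The formula sees only the total shift not due to treatment, so recovery or concomitant treatment of the same size has the same effect as practice.

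**Step 2: a true loss.** Assume a true MST-caused decline of 0.4 SD, with n = 30 and r = 0.7. The probability that the paired test detects a decline is 0.780 with no practice gain, 0.277 with a gain of 0.2 and 0.101 with a gain of 0.3.

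**Step 3: the randomised contrast.** Two-sample t-tests of change scores were simulated (30 per arm, r = 0.7, 20,000 runs) with the same gain in both arms. With no MST–ECT difference, the rejection rate is 0.048, 0.049 and 0.047 for gains of 0, 0.3 and 0.5. With a true difference of 0.4 SD, the mean estimate is 0.40 and power is 0.50 at every gain. A common gain cancels.

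**The case against.** The strongest reply is that the trial already has the right comparator. It is a randomised MST-versus-ECT study, and its side-effect hypothesis in section 4.4 is comparative. Section 14.2(2) can be read as comparing changes between the two interventions, and analysis of variance is among the listed methods. This largely stands. Nothing in the protocol says outright that a within-arm rise will be credited to MST. What remains is that objective 2 is not written as a contrast and section 14.2(2) does not name one, so the text permits the wrong reading.

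A reader might infer that practice gain could conceal cognitive harm in the trial's main safety comparison. The documents do not support that: Step 3 shows that an equal gain leaves the MST-minus-ECT difference unchanged. Only an absolute claim about one arm is exposed.

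A reader might also infer that section 6.1 is at fault and that controls should be retested, or that the lack of a stated parallel form is the defect. Neither follows. Healthy controls may learn more than acutely manic patients, and their retest would not remove recovery or concomitant treatment. The protocol's silence on test forms does not show that the same form is used, since that detail may sit in a procedure document. Even a parallel form would not make within-arm change interpretable, because practice is one component and is not shown to be the largest.

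Finally, the sizes rest on assumed gains and correlations. That is correct, and it is why a wide range is shown.

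**Conclusion.** The point holds as a mismatch between a one-arm causal objective and a design that supports only a comparative cognitive conclusion. Within-arm RBANS change cannot be attributed to MST or taken as absence of harm. Over the assumed ranges, the chance of a spurious significant improvement is about 16% to 92% against 2.5%. These figures illustrate the direction and possible size of the problem and are not estimates for this trial. The MST-minus-ECT difference is sound provided practice and recovery are similar in the two arms. RBANS is a secondary outcome and the comparative hypothesis is unaffected, so this is a worthwhile correction of wording and analysis, not a flaw in the randomised design.

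**What to change.** - In section 14.2(2), name the between-arm difference in RBANS change (MST minus ECT, adjusted for baseline RBANS) as the cognitive analysis.
- State there that within-arm before/after RBANS change is descriptive only and is not reported as an MST effect or as evidence of no harm.
- Reword the cognitive part of objective 2 to the MST-versus-ECT difference.
- Optional and secondary: use a parallel RBANS form at the second test, if the Chinese version has one. Section 6.1 can stay as it is with respect to control follow-up.

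**Cost.** No added visits or staff. Objective 2 becomes narrower, with no absolute cognitive claim for MST. The contrast is also less sensitive than a paired test: in Step 3, power for a 0.4 SD difference is 0.50 with 30 per arm. Baseline adjustment recovers part of this, since under the same assumptions the residual variance falls from 2(1−0.7) = 0.60 to 1−0.7² = 0.51. A non-significant difference should therefore be reported with its confidence interval and not as equivalence.

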## 6.2 Patients with Bipolar Mania

Inclusion criteria: ① meeting the diagnostic criteria by the fifth edition of the Diagnostic and Statistical Manual of Mental Disorders (DSM-5) and currently during a manic episode; ② inpatients in Shanghai Mental Health Center; ③ clinical indications of receiving convulsive treatment, such as severe psychomotor excitement or retardation, attempts of suicide, being highly aggressive, pharmacotherapy intolerance, and ineffectiveness of antipsychotics; ④ age between 18 and 55 years old; ⑤ moderate to severe manic symptoms with scores of Young Manic Rating Scale (YMRS)  $\geq 10$ ; ⑥ Written informed consent.

Exclusion criteria: ① comorbidity with other mental disorders by DSM-5; ② with unremovable metal implants; ③ a laboratory abnormality with an impact on the efficacy of treatments or safety; ④ severe physical diseases (stroke, heart failure, liver failure, neoplasm, or immune deficiency), a laboratory abnormality with an impact on the efficacy of treatments or safety; ⑤ Alcohol or substance dependence in the 30 days prior to the start of the trial or in the 6 months prior to the trial; ⑥ failure to respond to an adequate trial of ECT; ⑦ being or intending to get pregnant during the study; ⑧ other conditions that investigators consider to be inappropriate to participate in this trial.

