## 7. Sample Size

Due to the lack of previous MST study as an adjunctive treatment for bipolar mania, we estimated based on previous ECT study. The following formula was applied with  $\alpha=0.05$ ,  $\beta=0.80$ ,

$$n = 2\pi(1 - \pi) \left[ \frac{(u_{1-\alpha} + u_{1-\beta})}{\delta} \right]^2$$

The sample size is 30 for ECT and MST group, respectively.

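### Within-arm changes credited to MST, and differences between patients and drug-free controls, cannot be separated from the patients' concurrent drug treatment

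*Protocol*

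**What the plan says.** Controls (Protocol 6.1) must be people who "are not currently taking any medication". They are assessed once, at baseline, on RBANS, CI and resting-state fMRI. The section counts both TMS and MRS as part of the CI assessment. Matching is on sex, age, education and socio-economic status.

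Patients (6.2) are "inpatients in Shanghai Mental Health Center" in a current manic episode. The examples of indications for convulsive treatment include "pharmacotherapy intolerance, and ineffectiveness of antipsychotics". No inclusion or exclusion criterion asks for a drug-free period or a stable regimen, and no section listed in the table of contents deals with concomitant drugs.

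MST is called adjunctive twice: section 4.2 says that "there is currently no research exploring the use of MST as an adjunctive treatment for bipolar manic", and section 7 refers to the "lack of previous MST study as an adjunctive treatment for bipolar mania". ECT is not given that label, but it is delivered to the same population under the same criteria.

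Objective 2 (section 3) is "To investigate MST induced changes of brain plasticity and cognitive functions in patients with bipolar mania". Section 14.2(1) compares the MST, ECT and control groups at baseline. Section 14.2(2) compares clinical, "neurocognitive and CI measures before and after ECT and MST interventions". Section 14.2(3) hypothesises raised default-mode connectivity in mania that improves after either intervention. No stated analysis mentions drug treatment.

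**The concern.** Two attributions go beyond what the design can carry.

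The first is at baseline. Patients may be taking antimanic drugs and controls may take none. A difference in CI, cognition or connectivity is then a difference between treated mania and untreated health. Section 14.2(3) presents the expected connectivity difference as a feature of patients with mania.

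The second is over time. Treatment lasts up to four weeks. If drugs are started, changed or still taking effect in that period, the before-after difference within the MST arm contains their effect too, yet Objective 2 credits the change to MST. The controls have no second assessment, and no arm receives drugs alone, so nothing in the design supplies the change to subtract.

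At stake are Objective 2 and the mechanism part of Objective 3. A rise in CI could be reported as a mechanism of MST when some or all of it came from co-medication.

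**Working it through.** **Plan's own figure.** The only computed figure is 30 per arm (section 7). It cannot be reproduced, because the response rate and the difference in the formula are not given. This point does not depend on how it was derived; 30 is used below only as the arm size.

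**What each contrast can identify**

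| Contrast | Where | Differs between the sides | Can it isolate the named cause? |
|---|---|---|---|
| Patients v controls, baseline | 14.2(1) | Illness, and drugs wherever patients take them | No: with no medicated control, illness and drug effects are not separable |
| Before v after, MST arm | 14.2(2), Objective 2 | MST, time, and any drug effect over the course | No: there is no drugs-only arm and controls are not followed |
| MST v ECT, difference in change | Available from the randomisation (section 5) | Type of seizure therapy; baseline drugs balanced in expectation | Yes for the MST-ECT difference, subject to drug changes after allocation |

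The third row has a limit. Section 4.4 expects a mechanism common to MST and ECT. A change shared by both arms cancels in the randomised contrast, so that hypothesis falls back on the second row, where drugs are not separated.

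GABA needs care. Section 14.2 names it only for its within-group correlation with CI. It enters the group contrast only because section 6.1 counts MRS as part of CI.

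**Illustration of size.** The documents give no drug effect, no proportion medicated and no pre-post correlation. The shift d (in SD of the measure) and the correlation r below are assumptions. Each calculation supposes no illness or MST effect at all and uses a two-sided 5% normal approximation:

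chance of p<0.05 = 1 − Φ(1.96 − d/SE) + Φ(−1.96 − d/SE)

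*Before-after in one arm of 30:* SE = √[2(1 − r)/30].

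- r = 0.5: SE = √(1/30) = 0.183. For d = 0.3, d/SE = 1.64 and the chance is 38%.
- r = 0.7: SE = √(0.6/30) = 0.141. For d = 0.3, d/SE = 2.12 and the chance is 56%.

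*60 patients v 30 controls:* SE = √(1/30 + 1/60) = 0.224. For d = 0.3, d/SE = 1.34 and the chance is 27%.

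| Assumed mean drug shift | Before-after, r = 0.5 | Before-after, r = 0.7 | 60 v 30 at baseline |
|---|---|---|---|
| 0 | 5% | 5% | 5% |
| 0.2 SD | 20% | 29% | 15% |
| 0.3 SD | 38% | 56% | 27% |
| 0.5 SD | 78% | 94% | 61% |

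The shift is the group mean. It shrinks if only some patients are medicated or change drugs, and shifts in opposite directions can cancel.

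**The case against.** Unmedicated healthy controls are an ordinary choice and not an error. CI, MRS and fMRI are secondary outcomes, and section 4.4 says that mechanism will be explored. The primary outcome is YMRS reduction, in which controls play no part. Drug covariates can be left to a statistical analysis plan. Drug recording may sit in the case report form, whose contents are not shown, and the flow chart is missing from the text at hand, so silence does not prove that drugs go unrecorded.

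Most of that stands, and it limits the point. What it does not answer is the causal wording of Objective 2 and the absence of any comparator for drug effects. Those are protocol matters, and a later plan cannot separate illness from drugs when every control is drug-free.

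Several stronger readings are tempting but unsupported:

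- *A reader might infer that every patient is medicated and the control contrast is fully confounded.* The protocol does not say so. Medication is inferred from the adjunctive role, inpatient mania and the absence of a drug restriction. Patients with drug intolerance may be on little or nothing.
- *That many patients enter because antipsychotics failed.* This is one example in a list, with no frequency.
- *That unmasked clinicians will alter drugs differently by arm.* Neither the randomisation section nor the outcome section says anything on masking or drug changes. Divergence after allocation is possible, but not documented.
- *That drug drift would supply some fixed share of the detectable change.* Suppose half the patients change regimen and each change shifts the measure by 0.3 to 0.8 SD. The mean then moves by 0.15 to 0.40 SD, which is 29% to 78% of the detectable 2.80/√30 = 0.51 SD. That holds only if all shifts run the same way and r = 0.5. At r = 0.3 the range is about 25% to 66%, and at r = 0.7 about 38% to 101%. None of these inputs is in the documents.

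Adjusting for drug change is also no cure. It happens after randomisation and may follow response, so conditioning on it can introduce bias.

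**Conclusion.** The point holds in limited form. To the extent that patients are medicated, the baseline contrasts with controls describe illness plus treatment, and within-arm changes cannot be credited to MST alone. It does not undermine the primary YMRS comparison, and it does not show that the randomised MST-ECT difference is biased.

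The size is unknown. The 38% figure (0.3 SD shift, r = 0.5, 30 patients) shows only that a modest drug effect could produce a significant before-after result fairly often. The conclusion rests on three readings of the protocol: that adjunctive means given on top of other treatment, that no drug restriction applies, and that Objective 2 is to be answered from before-after change. It is worth acting on because the remedy is cheap and alters what the trial may claim.

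**What to change.** 1. At each CI, MRS, fMRI and RBANS assessment, record drug class and daily dose from the inpatient chart. Report drugs and drug changes by arm.
2. In 14.2(1), describe the patient-control difference as that of treated mania. Report associations of the measures with drug class and dose within patients as exploratory.
3. In 14.2(2), base MST-specific statements on the randomised MST-versus-ECT difference in change. Reword Objective 2 to changes during adjunctive MST compared with adjunctive ECT. Say that a change common to both arms cannot be separated from concurrent drugs.
4. Treat any analysis adjusted for drug change, or limited to patients whose regimen did not change, as exploratory only. State that drug change comes after randomisation and may depend on response, so such an analysis does not isolate the MST effect.

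The cost is one drug record per assessment and a narrower mechanism claim. The exploratory analyses will be imprecise with 30 per arm. No drug rule is proposed and patient care does not change.
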